**Template Instructions**

***Sections that do not apply:***

- In several sections, the addition of checkboxes for **Not Applicable** have been added to the template as responses.
  - If an N/A checkbox is present, select the appropriate justification from the list.
  - If an N/A checkbox is not present, or if none of the existing checkboxes apply to your study, you must write in your own justification.
- In addition:
  - For research where the only study procedures are records/chart review: Sections 19, 20, 22, 23, 24, 25, 31, and 32 do not apply.
  - For exempt research: Sections 31 and 32 do not apply.

**Studies with multiple participant groups:**

- If this study involves multiple participant groups (e.g. parents and children), provide information in applicable sections for each participant group. Clearly label responses when they differ. For example:

Response:

Intervention Group:

Control Group:

**Formatting:**

- Do not remove template instructions or section headings when they do not apply to your study.

If you are pasting information from other documents using the “Merge Formatting” Paste option will maintain the formatting of the response boxes.

**Amendments:**

- When making modifications or revisions to this and other documents, use the **Track Changes** function in Microsoft Word.
- Update the version date or number **on Page 3.**

**GRANT APPLICABILITY:**

*Indicate whether this protocol is funded by a grant (e.g. NIH, foundation grant). For a grant with multiple aims, indicate which aims are covered by this research proposal.*

[figure not shown]
*NOTE: This question does not apply to studies funded by a sponsor contract.*

*Include a copy of the grant proposal with your submission.*

Response:

This project has is not funded. Grant applications are planned after the preliminary analyses are conducted.

RESEARCH REPOSITORY:

*Indicate where the research files will be kept, including when the study has been closed. The repository should include, at minimum, copies of IRB correspondence (approval, determination letters) as well as signed consent documents. This documentation should be maintained for 3 years after the study has been closed.*

Response:

Location: Kapoor 355

Address: South Campus, University at Buffalo

Department: Pharmaceutical Sciences

No patient recruitment – signed consents not applicable.

# Objectives

- 1. Describe the purpose, specific aims, or objectives of this research.

Response:

Fatigue is a very frequent MS symptom that affects greater >75% of patients [^1-3^](#_ENREF_1) [^4^](#_ENREF_4). Fatigue adversely affects MS patients’ quality of life and activities of daily living [^2^](#_ENREF_2)^,^ [^5^](#_ENREF_5). Fatigue worsens with MS disease progression and makes it more difficult for people with MS to adapt to their chronic disease [^6^](#_ENREF_6).This Supplementary Study will build on the important pioneering work by [name] on the modified Paleolithic diet in MS, which is known as the Wahls’ Elimination Diet. It will leverage clinical samples collected in the course of [name] currently funded National Multiple Sclerosis Society-funded clinical study to assess the role of metabolism in fatigue and from the smaller longitudinal study (n = 20) of multimodal interventions (combination of Paleolithic diet with supplements plus stretching, strengthening, meditation and massage) to reduce fatigue. We will compare the effects of Usual Diet vs. Swank Diet vs. Wahls’ Elimination Diet on fatigue in MS patients. We will compare baseline vs. 12 month follow-up samples ( in the multimodal study.

The cholesterol pathway is important for immune responses and neuronal functions in the central nervous system. The aims of this clinical study are to delineate the molecular mechanisms and to characterize the relationships between the cholesterol pathway and fatigue in multiple sclerosis (MS).

From our research, there is compelling evidence that adverse cholesterol profiles are associated with MS disease progression. The pathophysiological mechanisms mediating these adverse associations in MS are not known. Our strategy for dissecting the underlying pathophysiological mechanisms is to target molecular mediators of the inter-dependence between CNS and peripheral cholesterol homeostasis in MS patients. Based on our results, we hypothesize that the associations between dietary changes and fatigue are mediated by metabolic changes that are reflected in serum cholesterol serum cholesterol and are driven by key contributions from oxysterols, which are a promising class of endogenous cholesterol metabolites and signaling molecules capable of: i) crossing the blood brain barrier (BBB) and, ii) regulating the homeostasis between CNS and peripheral cholesterol.

We will systematically investigate the oxysterols 24-hydroxycholesterol (24HC), 27-hydroxycholesterol (27HC), 7α-hydroxycholesterol (7αHC) and 7-ketocholesterol (7KC) because they are potent transcription factor ligands and regulatory mediators of cholesterol and immune homeostasis. These oxysterols have been shown to modulate the interactions between immune cells and the vascular cells of the BBB and CNS pathophysiology.

**Specific Aim 1 >** Characterize the longitudinal changes in lipid profile occuring during the “Usual Diet Phase” and in the Swank Diet and Wahls’ Elimination Diet groups.

For this aim, a comprehensive lipid profile will be obtained. The profile will consist of: i) overall lipid profile, ii) serum free fatty acid and lipoprotein cholesteryl ester fatty acid profile, iii) apolipoprotein profile, iv) serum paraoxonase activities, serum paraoxonase genotype and C-reactive protein level, and v) serum oxysterol profile.

**Specific Aim 2 >** Investigate the associations if any, between the observed changes in lipid profile in Aim 1 and fatigue outcomes. Identify the lipid profile biomarkers that are most strongly associated with fatigue outcomes in MS. Assess whether these lipid profiles changes are potential mediators of the effects of diet on fatigue.

When successfully completed, this project will identify and characterize important molecular mechanisms that could explain the pathophysiological impact of the cholesterol pathway on MS fatigue. The findings can be leveraged for targeting therapeutic and lifestyle-based intervention strategies to reduce fatigue in MS patients.

- 1. State the hypotheses to be tested, if applicable.

NOTE: A hypothesis is a specific, testable prediction about what you expect to happen in your study that corresponds with your above listed objectives.

Response:

**Hypothesis 1 >** The Wahls’ Elimination Diet is associated with significant improvements in the lipid profile including decreased total cholesterol, decreased low density cholesterol (LDL-C) and apolipoprotein B (ApoB) and increases in high density cholesterol (HDL-C), decreases in cholesteryl esters conjugated with saturated fatty acids and decreased CRP levels. The Wahls’ Elimination diet increases 24-hydroxycholesterol (24HC) and decreases 7-ketocholesterol (7KC) levels.

**Hypothesis 2 >** The improvements in the lipid profile are mediators of benefits of the Wahls’ Elimination Diet on fatigue. Subjects with greater improvements in their lipid profile will exhibit greater improvements in fatigue outcomes.

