# Study Design

- 1. Describe and explain the study design (e.g. case-control, cross-sectional, ethnographic, experimental, interventional, longitudinal, observational).

Response:

Our study will analyze blood samples from [name] prospective study and her completed multimodal study.

[name] study has a prospective, longitudinal, 36-week-long, randomized, parallel group study design in which MS patients will be randomized from a lead-in “Usual Diet Phase” to either the Swank Diet or the Wahls’ Elimination Diet.

The primary outcome is fatigue as measured on the Fatigue Severity Scale and Modified Fatigue Impact Scale.

The study has 4 visits over 36 weeks with each visit being 12 weeks apart. There will be a 12-week-long lead-in “Usual Diet Phase” to assess the ability of enrolled subjects to complete daily food records and collect fatigue and other health data while participants are consuming their usual diet.

The subjects who satisfactorily complete food records at Visit 1 will continue into the Intervention phase of the study at Visit 2 (Week 12) and be randomized to either the Swank Diet or the Wahls’ Elimination Diet.

The subjects and their adult companion (if present) will be trained at Visit 2 on the relevant study diet by a Registered Dietitian Nutritionist who will then call the subject weekly for 4 weeks to provide coaching and support for adhering to the study diet. The final coaching call will occur at Month 2.

The subject will return at Week 24 (Visit 3) and Week 36 (Visit 4). Dietary assessments will include a food frequency questionnaire and a 24-hour weighed food records. The assessments will include motor assessments, symptom questionnaires and dietary assessments.

Motor assessments will include a 6-minute walk test, 25-foot walk test, 9-hole peg board to test hand function and symbol digit test to testing cognitive function. Questionnaires to assess fatigue, quality of life and medical diagnoses are also included in the assessments. The assessments will be completed on or around each study visit.

The longitudinal multimodal study is already completed. The intervention investigated to reduce fatigue in this study was multimodal (combination of Paleolithic diet with supplements plus stretching, strengthening, meditation and massage).

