# Data Management and Analysis

- 1. Describe the data analysis plan, including any statistical procedures. This section applies to both quantitative and qualitative analysis.

Response:

The demographic, clinical and biomarker data will be centrally organized in a relational database (e.g., Access) and exported for statistical analysis. Range and consistency checks will be performed to identify errors. SPSS Statistics (IBM) will be used. We will assess descriptive statistics, distributions and pairwise correlations to inform analyses. A systematic hierarchical approach to analysis will be employed given the number of oxysterols, clinical and fatigue measures. Analyses will correct for multiple testing using the Benjamini-Hochberg method [20](#_ENREF_20).

Where necessary, clinical thresholds from the National Cholesterol Education Program Guidelines [32](#_ENREF_32) of HDL < 40, LDL-C ≥ 130, and TC ≥ 200 mg/dl will be used to create indicator variables for classifying subjects with low HDL-C, high LDL-C and high TC, respectively; hypercholesterolemia will be defined as TC ≥ 240 mg/dl. Appropriate regression analyses will be used for assessing associations of cholesterol biomarker and the clinical and fatigue variables (dependent variables). Count variables, e.g., relapse rate, will be analyzed with negative binomial regression. Ordinal regression will be used for EDSS.

Several clinically relevant questions will be addressed in the analyses. We expect the cholesterol profiles to differ between the Usual Diet phase vs. Swank Diet vs. Wahls’ Elimination Diet groups. The effects of diet on individual apolipoproteins, CRP and paraoxonase and other markers will also be investigated. Likewise, we will investigate whether oxysterol levels differ between the Usual Diet, Swank Diet and Wahls’ Diet groups? Given the longitudinal design we will also be able identify those oxysterols whose changes are associated with changes in lipid profile variables.

Since we hypothesize that decreased 24HCand increased 7KC are associated with greater neurodegeneration in MS, our primary analysis will evaluate the associations of changes in these oxysterols in the Usual Diet, Swank Diet and Wahls’ Elimination Diet groups. The interpretation framework was noted previously: 24HC is a marker of CNS cholesterol metabolism and 7KC is a marker of oxidative stress.

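### Aim 2 promises the lipid markers most strongly tied to fatigue, but Benjamini-Hochberg neither shows how uncertain that ordering is nor corrects estimates picked for being largest

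*Protocol*

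**What the plan says.** Specific Aim 2 (Protocol, section 1.0 Objectives) has three parts: to investigate associations between the lipid changes of Aim 1 and fatigue, to "Identify the lipid profile biomarkers that are most strongly associated with fatigue outcomes in MS", and to "Assess whether these lipid profiles changes are potential mediators of the effects of diet on fatigue". Section 2.0 makes marker-fatigue associations the primary goals, so this is a main product of the study.

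The candidate list is wide. Under Aim 1, "For this aim, a comprehensive lipid profile will be obtained". It covers overall lipids, free and cholesteryl ester fatty acids, apolipoproteins, paraoxonase measures with C-reactive protein, and oxysterols, of which four are named. For the parent randomised study, section 4.0 says: "The primary outcome is fatigue as measured on the Fatigue Severity Scale and Modified Fatigue Impact Scale". That gives at least two fatigue scales.

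On multiplicity, section 17.0 states: "Analyses will correct for multiple testing using the Benjamini-Hochberg method". The sentence before it announces a systematic hierarchical approach, without giving its order or rules. The section also singles out 24HC and 7KC for a primary analysis across the diet groups, in a sentence that names no fatigue outcome. The power item is answered as not applicable. No sample size is given for the randomised study; the only size stated is for samples "from the smaller longitudinal study (n = 20) of multimodal interventions".

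**The concern.** Saying which markers are strongest is a different task from saying which are associated at all. Benjamini-Hochberg serves the second task. It controls the expected share of false positives among the markers declared significant. It gives no measure of how easily the order could change in another sample. It also does nothing to estimates that reach the top partly because chance pushed them upward, and passing a significance filter adds to that bias.

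Correlated markers with similar modest effects make the order least stable, and a lipid panel may well be of this kind. The protocol expects its findings to guide therapeutic and lifestyle interventions, and grant applications are to follow the preliminary analyses. A marker named as strongest when its lead is within sampling error, with an overstated association, could misdirect both.

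**Working it through.** The protocol gives no n, effect size or marker count for Aim 2, so there is no figure of its own to reproduce. The check is a simulation under stated assumptions.

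**Inputs from the protocol:** a five-class panel (section 1.0), two fatigue scales (section 4.0), Benjamini-Hochberg (section 17.0).

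**Assumed inputs:** multivariate normal data with one marker value and one fatigue value per patient; number of markers, their mutual correlation, true r and n as shown; Benjamini-Hochberg level 5%, since no level is stated.

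**Step 1. Ordering and overstatement.** In each simulated sample, compute r for every marker and pick the largest |r|. Record whether it is the truly best marker, its observed |r| and its true r. The best marker has r = 0.30, all others 0.15, and mutual correlation is 0.3.

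| Markers | n | Top marker truly best | Observed \|r\| | True r of marker chosen |
|---|---|---|---|---|
| 30 | 40 | 20% | 0.43 | 0.18 |
| 30 | 80 | 36% | 0.36 | 0.20 |
| 11 | 80 | 54% | 0.34 | 0.23 |
| 30 | 200 | 71% | 0.31 | 0.26 |

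The last column follows from the third: true r = P × 0.30 + (1 − P) × 0.15. For 30 markers at n = 80, 0.36 × 0.30 + 0.64 × 0.15 = 0.108 + 0.096 = 0.204. At n = 200, 0.71 × 0.30 + 0.29 × 0.15 = 0.213 + 0.0435 = 0.2565.

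The overstatement is the ratio of observed to true: 0.36 / 0.20 = 1.8 at n = 80 and 0.31 / 0.26 = 1.19 at n = 200.

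**Step 2. Does Benjamini-Hochberg remove it?** A second model is kinder to the plan: 25 markers, exactly one with a true effect of r = 0.30, mutual correlation 0 or 0.3. The last two columns cover only samples in which at least one marker passes.

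| n | Top marker correct, all samples | Top marker correct, given a pass | Mean top \|r\|, given a pass |
|---|---|---|---|
| 60 | 46–56% | 66–83% | 0.44–0.45 |
| 80 | 62–69% | 76–92% | 0.40 |
| 100 | 68–77% | 81–93% | 0.37 |
| 200 | 94–97% | 95–99% | 0.31 |

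So the filter helps to find the right marker but does not correct its size. At n = 80 the reported value averages 0.40 when the largest true value is 0.30, a ratio of 0.40 / 0.30 = 1.33.

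**Step 3. Sensitivity to effect size.** In the second model at n = 80, the top marker is correct in 29–33% of samples when the single true r is 0.2, and in 87–91% when it is 0.4.

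**Step 4. Does the remedy work?** Resample patients and repeat the whole screen in each resample. The optimism is the average, over resamples, of the winner's |r| in the resample minus the same marker's |r| in the full data. Subtract it from the observed |r|. In the 30-marker setting at n = 80, this brings the estimate from 0.36 to about 0.23, against a true 0.20.

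**The case against.** The strongest reply is that the harm depends on assumptions. The size of the randomised study is not given. With a large sample, or one clearly dominant marker, the top marker is usually right and little overstated. That stands, and it means the error rates cannot be stated flatly. It is also fair that the aim speaks of markers in the plural and prescribes no ranking procedure, that a wrong pick in Step 1 is still a real correlate (r = 0.15), and that the simulations use one observation per patient while the plan foresees repeated-measures regression.

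A second reply is that resampling details belong in a statistical analysis plan, which is not shown here. That holds for the details. But the protocol itself sets the goal of naming the strongest markers and itself names the multiplicity tool, and that tool does not serve the goal.

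Four stronger readings are tempting, and the documents do not support them:

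- **That the main sample is small.** Its size is not stated. The n = 20 belongs to the separate multimodal study.
- **That Benjamini-Hochberg is the only safeguard.** Section 17.0 also announces a hierarchical approach and names 24HC and 7KC in advance for a primary analysis. The hierarchy is undefined and the 24HC/7KC sentence names no fatigue outcome, so neither settles the ordering, but both are there.
- **That mediators are chosen by rank, so selection bias carries into the mediation step.** In "Assess whether these lipid profiles changes are potential mediators of the effects of diet on fatigue" the changes meant are most naturally those of Aim 1, and Hypothesis 2 speaks of the lipid improvements that Hypothesis 1 lists.
- **That the multimodal study could serve as validation.** At n = 20 a true r of 0.30 has about 25% power, and an observed 0.30 has a 95% interval of about −0.16 to 0.66. Its intervention also added supplements, exercise, meditation and massage. Agreement or disagreement would say little.

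The protocol's hedges (associations, if any; potential mediators) soften the mediation claim. They do not soften the promise to identify the strongest markers.

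**Conclusion.** The point holds as a mismatch between goal and method: Aim 2 promises an ordering, and the named correction controls false discoveries only. Under the 30-marker assumptions the top marker is truly best in about 36% of samples at n = 80 (observed |r| 0.36, true 0.20) and about 71% at n = 200 (0.31, true 0.26). With a single true marker of r = 0.30 and Benjamini-Hochberg applied, identification is better, but the reported size is still about a third too high at n = 80; at n = 200 the excess nearly vanishes (0.31 against 0.30). These figures rest on assumed n, marker count, correlations and effects, none of which the protocol gives. They show that the problem can be material, not that it must be. The change is worth making because it reports the uncertainty at whatever n applies.

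**What to change.** In section 17.0, add for Aim 2:

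1. Draw bootstrap samples of patients (for example 1,000), keeping each patient's visits together, and repeat the whole marker screen in each one.
2. Beside the Benjamini-Hochberg results, report optimism-corrected associations and a 95% interval for each marker's rank.
3. Call a marker strongest only where its rank interval supports that. Otherwise label the result hypothesis-generating.

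The cost is some programming and about a paragraph of text, with no new patients or samples. The downside is that reported associations will be smaller and fewer markers can be called strongest. If the sample proves large, the rank intervals will tend to be narrow and little is lost.

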# Scientific Endpoints

*2.1* Describe *the scientific endpoint(s), the main result or occurrence under study.*

*NOTE: Scientific endpoints are outcomes defined before the study begins to determine whether the objectives of the study have been met and to draw conclusions from the data. Include primary and secondary endpoints. Some example endpoints are: reduction of symptoms, improvement in quality of life, or survival. Your response should* ***not*** *be a date.*

Response:

The primary goals are to study the associations of cholesterol biomarkers and oxysterol profiles with quantitative fatigue measures obtained in the Wahls study.

# Study Design

- 1. Describe and explain the study design (e.g. case-control, cross-sectional, ethnographic, experimental, interventional, longitudinal, observational).

Response:

Our study will analyze blood samples from [name] prospective study and her completed multimodal study.

[name] study has a prospective, longitudinal, 36-week-long, randomized, parallel group study design in which MS patients will be randomized from a lead-in “Usual Diet Phase” to either the Swank Diet or the Wahls’ Elimination Diet.

The primary outcome is fatigue as measured on the Fatigue Severity Scale and Modified Fatigue Impact Scale.

The study has 4 visits over 36 weeks with each visit being 12 weeks apart. There will be a 12-week-long lead-in “Usual Diet Phase” to assess the ability of enrolled subjects to complete daily food records and collect fatigue and other health data while participants are consuming their usual diet.

The subjects who satisfactorily complete food records at Visit 1 will continue into the Intervention phase of the study at Visit 2 (Week 12) and be randomized to either the Swank Diet or the Wahls’ Elimination Diet.

The subjects and their adult companion (if present) will be trained at Visit 2 on the relevant study diet by a Registered Dietitian Nutritionist who will then call the subject weekly for 4 weeks to provide coaching and support for adhering to the study diet. The final coaching call will occur at Month 2.

The subject will return at Week 24 (Visit 3) and Week 36 (Visit 4). Dietary assessments will include a food frequency questionnaire and a 24-hour weighed food records. The assessments will include motor assessments, symptom questionnaires and dietary assessments.

Motor assessments will include a 6-minute walk test, 25-foot walk test, 9-hole peg board to test hand function and symbol digit test to testing cognitive function. Questionnaires to assess fatigue, quality of life and medical diagnoses are also included in the assessments. The assessments will be completed on or around each study visit.

The longitudinal multimodal study is already completed. The intervention investigated to reduce fatigue in this study was multimodal (combination of Paleolithic diet with supplements plus stretching, strengthening, meditation and massage).

